
### Study design and setting

The trial is an open-label, randomised, controlled superiority trial recruiting adults who are undergoing elective primary lower-limb arthroplasty with sedation by propofol infusion by effect-site targeting into two equal-sized parallel arms: PMPS and ACPS. The study will be run as a single-centre study at Nottingham University Hospitals National Health Service (NHS) Trust. The trial will be conducted only in a secondary care setting.

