### Enrolment

Patient screening for eligibility and recruitment will be conducted at the Theatre admission lounge, Nottingham City Hospital campus. This site is where our patients are usually treated. Screening will be performed by the supervising clinical anaesthetist during their routine pre-operative patient assessment. The supervising clinical anaesthetist will notify a study investigator of potentially eligible patients. The recruited patient will sign and date the approved version of the informed consent form before any procedures specific to the clinical investigation are performed.

The participant’s research data will be gathered during a single visit to hospital, which forms part of usual clinical care. A telephone consultation between a study investigator and each participant will be performed at post-operative day 7–10.

After enrolment, the participant will be given a group-specific laminated educational leaflet explaining their sedation system. Those allocated to PMPS will receive written instructions on the use of the PMPSD and those allocated to ACPS will receive written explanation on how their supervising clinical anaesthetist will sedate them.

A pre-operative questionnaire will be administered to all participants before they are taken to the anaesthetic room. The following data will be recorded: age, gender, whether hip or knee arthroplasty, surgeon initials, supervising clinical anaesthetist initials, patient weight and height, American Society of Anaesthetist Physical Status Classification, respiratory rate, arterial oxygen saturations, heart rate, blood pressure (systolic, diastolic, mean) and sedation score on the Modified Observer’s Assessment of Alertness/Sedation (mOAA/S) Scale.

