### Statistical methods

Propofol consumption (milligrams) will be calculated in participants randomised to the two study groups. Body weight (kilograms) and height (centimetres) recorded at the pre-operative assessment will be used. Length of sedation is defined as the time from when the propofol sedation is commenced by the supervising clinical anaesthetist up until the time when the first skin clip is inserted to close the wound (at which point the anaesthetist will stop the sedation).

The alternative hypothesis is two-sided. The level of statistical significance is 5%. The clinical superiority of PMPS over ACPS will be shown if the mean rate is reduced by 29% (or more) when using PMPS, compared with ACPS. The randomisation schedule will be computer-generated using an 8-block design, with allocation advised by opaque sealed envelope. The expected recruitment rate into the study is 2 patients per week.

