### Randomisation

Enrolled participants will be randomised by block randomisation technique. An opaque sealed envelope randomisation system will be used. Allocation concealment will be achieved by the generation of an unpredictable allocation sequence into sealed envelopes by an independent party, which will not be opened until patient consent for inclusion has been obtained. This will be accessed by a study investigator for the purposes of allocation. Randomisation will be conducted on the day of surgery.

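### A single disclosed block size in an open-label, single-centre envelope trial leaves about one allocation in five (or one in six) certain to anyone who knows it and tallies, so the sequence is not unpredictable as claimed

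*Protocol article*

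**What the plan says.** The protocol article describes allocation in two places.

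- Statistical methods: "The randomisation schedule will be computer-generated using an 8-block design, with allocation advised by opaque sealed envelope".
- Randomisation: "Enrolled participants will be randomised by block randomisation technique", and "Allocation concealment will be achieved by the generation of an unpredictable allocation sequence into sealed envelopes by an independent party". The envelopes stay closed until consent has been obtained. Of the envelope system the section says "This will be accessed by a study investigator for the purposes of allocation". Randomisation takes place on the day of surgery.

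The setting is given elsewhere. Under Study design and setting, "The trial is an open-label, randomised, controlled superiority trial", run at one centre, with "two equal-sized parallel arms: PMPS and ACPS". Under Enrolment, "Screening will be performed by the supervising clinical anaesthetist during their routine pre-operative patient assessment", and that anaesthetist then tells a study investigator about possible candidates. The Discussion (Trial blinding) says that neither the clinical team nor the investigator collecting intra-operative data is blinded, and that the clinical team is independent of the trial team.

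The article names no second block size. It does not say that the block size is kept from the people who recruit, and it prints the block design itself.

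**The concern.** A permuted block with equal arms must end balanced. Once one arm has used its share of a block, every remaining allocation in that block is fixed. In an open-label trial with one known block size, past allocations reveal when that point is reached. Sealing the next envelope does not hide what it must contain.

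What is at stake is the choice of who enters and when. A person who knows the next arm can refer or approach a patient, or not, with that arm in mind. The primary outcome is propofol use per kilogram per hour, and anxiety is a secondary outcome. Selection on how anxious a patient seems, or how much sedation they are likely to want, could therefore bear on the comparison. Adjustment for recorded baseline variables can reduce such bias for measured factors, but not reliably for unmeasured ones.

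**Working it through.** **Inputs.** Allocation is 1:1 (Study design and setting). The block design is the 8-block one (Statistical methods), read either as blocks of 8 or as eight blocks of 10, since 8 × 10 = 80. The total is 80 randomised (Sample size calculation). Expected recruitment is 2 patients a week (Statistical methods). One unstratified list is an assumption; the article is silent on stratification.

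**The plan's own figure.** The article gives no figure for predictability. Its sample size does reproduce: exact power for Welch's test with means 1.580 and 2.231 and SDs 0.755 and 0.915 is 0.892 at 35 per arm and 0.901 at 36 per arm. That gives 72, and 72 / 0.9 = 80. The present point does not affect it.

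**Certain allocations, blocks of 8.** There are C(8,4) = 70 equally likely blocks. The number of allocations at the end of a block that are already fixed is distributed as follows:

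| Certain allocations | Blocks of 70 | Share |
|---|---|---|
| 1 | 40 | 57.1% |
| 2 | 20 | 28.6% |
| 3 | 8 | 11.4% |
| 4 | 2 | 2.9% |

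Mean = (40×1 + 20×2 + 8×3 + 2×4) / 70 = 112 / 70 = 1.6 per block. The closed form for block size B agrees: B / (B/2 + 1) = 8 / 5 = 1.6. As a share this is 1.6 / 8 = 20%. Ten blocks make 80 patients, so 10 × 1.6 = 16.

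**Certain allocations, eight blocks of 10.** 10 / 6 = 1.67 per block, or 16.7%. Over eight blocks, 8 × 1.67 = 13.3 of 80.

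**Best guess over all positions.** The strategy is always to guess the arm with more places left in the block. With m = B/2, the expected number of correct guesses is m + (2^(2m) / C(2m, m) − 1) / 2.

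- B = 8: 4 + (256/70 − 1)/2 = 5.33, and 5.33 / 8 = 66.6%.
- B = 10: 5 + (1024/252 − 1)/2 = 6.53, and 6.53 / 10 = 65.3%.

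A sequence that could not be predicted would give 0% certain and 50% correct guesses.

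**Effect of varying the block size.** Sequences of 80 were simulated with sizes drawn at random, for an observer who knows the set of sizes but not their order.

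| Scheme | Certain | Best guess correct |
|---|---|---|
| Fixed 8 | 20% | 67% |
| Mixed 4/6/8 | about 2% | about 68% |
| Mixed 8/10/12 | about 1% | about 65% |

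Varying the size removes nearly all certainty. It leaves guessing about where it was, and larger sizes lower it only slightly.

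**Ease of tallying.** At 2 patients a week, a block of 8 fills in about 8 / 2 = 4 weeks, and one of 10 in about 5 weeks.

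**The case against.** The strongest reply is that the article already names sound safeguards: "generation of an unpredictable allocation sequence into sealed envelopes by an independent party", opaque envelopes, opening only after consent, and randomisation on the day of surgery. Patients are already listed for surgery, so holding one back for a later envelope is harder than it would be in a clinic. This stands as far as it goes. These steps protect the individual envelope and limit delay. They do not stop prediction from earlier allocations, and not referring or not approaching a patient remains possible.

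Several stronger readings are tempting, and the document does not support them.

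- *Anyone on the team can predict one allocation in five.* The figure applies to a person who knows the block size and sees every allocation in order. The anaesthetist's initials are recorded for each patient, which suggests several anaesthetists, each perhaps seeing only some allocations.
- *The investigator who enrols also opens the envelope.* The article has a study investigator in each role but does not say that it is the same person.
- *The list is unstratified.* The article does not say so; here it is an assumption.
- *The anaesthetist's control of dosing in the ACPS arm is part of this problem.* That is a separate feature of an open-label comparison and does not depend on the block size.
- *Bias occurred, or has a known size.* Nothing in the article shows that anyone used such knowledge, and no shift in mg/kg/h can be derived from it.

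**Conclusion.** The point holds as a modest, correctable design weakness. One disclosed block size in an open-label, single-centre, 1:1 envelope trial contradicts reliance on an unpredictable sequence. On average 20% of allocations (about 16 of 80) are certain in advance with blocks of 8, or 16.7% (about 13 of 80) with eight blocks of 10. On either reading every block ends with at least one certain allocation.

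The figures assume a single unstratified list and an observer who knows the block size and tallies all earlier allocations. The unblinded study investigators are the people best placed to do that. The arithmetic is firm; whether any bias followed is unknown.

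**What to change.** Have the independent party generate the list, or replace any envelopes still unused, with randomly varying block sizes, and withhold the sizes from investigators and anaesthetists. A set such as 4/6/8 brings certain allocations down to about 2%, even if the set becomes known. It should not be presented as a cure for guessing, which stays at about 68% against 67% now. A larger set such as 8/10/12 brings it only to about 65%. The article should also say whether the 8 is a block size or a number of blocks.

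The cost is regenerating the list and envelopes, and a possible final imbalance of a few patients. If recruitment is complete, the final report should give the block structure, say who knew it, and qualify the word unpredictable.

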### Sample size calculation

Our calculation is based on results from a pilot PMPS study (*n* = 26) and prospectively gathered standard care ACPS (*n* = 17), showing that the mean body-weight-normalised rate of propofol consumption in the PMPS and ACPS groups was 1.580 (SD = 0.755) and 2.231 (SD = 0.915), respectively. For power of 90% and level of significance of 5% against the two-sided alternative hypothesis, 72 participants are required to detect the observed difference in mean rate using Welch’s two-sample *t* test. Expecting 10% drop-out of participants, a sample size of 80 is required. Participants who drop out from the trial prior to randomisation will be removed from the study and any trial data that may have been collected on them or from them will be destroyed. All participants dropping out after randomisation will be included in the study by intention to treat and all trial data collected up to the moment of drop out will be retained for analysis.

### Randomisation

Enrolled participants will be randomised by block randomisation technique. An opaque sealed envelope randomisation system will be used. Allocation concealment will be achieved by the generation of an unpredictable allocation sequence into sealed envelopes by an independent party, which will not be opened until patient consent for inclusion has been obtained. This will be accessed by a study investigator for the purposes of allocation. Randomisation will be conducted on the day of surgery.

### Statistical plan

All data collected will be summarised for reporting purposes using descriptive statistics. The hypothesis test associated with the primary outcome will compare the two mean consumption rates using standard statistical tests chosen appropriate to underlying assumptions (e.g. two-sample *t* test and the Wilcoxon-Mann-Whitney test). Testing will be performed using datasets formed according to inclusions based on intention to treat. *P* values will be reported, with values less than 5% declared statistically significant.

We will report analyses of secondary outcomes for complete cases that contain no major clinical investigation plan violations. Amongst these, button-press data will be modelled using count data regression methods, with extension to bivariate models to distinguish between successful presses and unsuccessful presses. The panel time-series of propofol consumption rates collected throughout the sedation period alongside button presses will together be modelled using marked-point process methods. Ordinal responses recorded on a Likert scale (peri-operative anxiety, patient satisfaction) will be compared across trial arms using parametric methods suitable to underlying assumptions and non-parametric methods, such as the Wilcoxon rank sum test. Preoperative and post-operative quality of recovery total scores will be compared using the Wilcoxon matched pairs test. Inter-item correlations will be computed and associations between scored items will be compared using Spearman rank correlation. The Bonferroni correction to allow for multiple comparisons will be applied. Qualitative data obtained from structured questions will be coded and computer-analysed. Any missing outcome data will be imputed using either a last-observation-carried-forward rule or, for the subset of comparable secondary outcomes, use data routinely measured and recorded as part of usual clinical care.

Health economic analysis aims to establish the net monetary benefit due to the NHS from introducing PMPS compared to the current practice of ACPS. Economic modelling will rely on parameterisations developed from the data gathered from all trial outcome measures, including health-related quality of life from the Euroqol (EQ)-5D-5 L questionnaire before/after data. These data will be collected as part of the pre-operative and post-operative participant interviews. Cost differentials across the two trial arms are expected due to propofol use and time to fitness for discharge from PACU.

No interim analyses are planned for this study. Any deviation from the original statistical plan will be described and justified in the final report.

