### Trial intervention

Propofol 1% is licensed in the UK for “Sedation for diagnostic and surgical procedures, alone or in combination with local or regional anaesthesia in adults and children > 1 month” [14]. The trial will be using propofol within the terms of this license. Patients randomised to PMPS will receive propofol according to the following algorithm: the effect-site target concentration of propofol will be commenced at 0.5 μg.mL^− 1^ and increased by 0.2 μg.mL^− 1^ (when the patient presses the button) to a maximum of 2.0 μg.mL^− 1^. Following a successful button-induced increase in the effect-site target, further button presses will not increase the target concentration for 2 min (this is termed the *lockout period*). If patients do not press the button for 15 min, the effect-site target will reduce by 0.1 μg.mL^− 1^, and will continue to reduce by 0.1 μg.mL^− 1^ every 15 min to a minimum of 0.5 μg.mL^− 1^ in the absence of a button-press. Patients randomised to ACPS will receive propofol according to the following algorithm: the effect-site concentration will be commenced at a level determined by the supervising clinical anaesthetist and incremented and decremented by them as they see fit. No maximum or baseline levels will be pre-specified. This constitutes standard clinical practice. Both groups will use Schnider effect-site TCI modelling.

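### The hypothesis, criterion and sample size rest on means and Welch's t test, but the primary test is left open and may be a rank test that does not address the mean

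*Protocol article*

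**What the plan says.** Four places in the protocol article bear on the primary test.

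- **Study objectives** and **Statistical methods** set the hypothesis and the superiority criterion on the mean rate of propofol consumption (mg/kg/h), with a reduction of at least 29%. On direction, "The alternative hypothesis is two-sided", and the significance level is 5%.
- **Sample size calculation** uses pilot means of 1.580 (SD 0.755) for PMPS and 2.231 (SD 0.915) for ACPS. It gives 72 participants as "required to detect the observed difference in mean rate using Welch’s two-sample" t test, raised to 80 for 10% drop-out.
- **Statistical plan** says the primary hypothesis test will "compare the two mean consumption rates using standard statistical tests chosen appropriate to underlying assumptions". Its examples are the two-sample t "test and the Wilcoxon-Mann-Whitney test". Welch's test is not named there. The section gives no decision rule, no order between the tests and no time at which the choice is made.
- **Enrolment** lists "age, gender, whether hip or knee arthroplasty, surgeon initials, supervising clinical anaesthetist initials, patient weight and height" among the data recorded before surgery. Neither test named in the Statistical plan uses any of these.

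**The concern.** The design sections commit to one quantity, the difference in means, and to one test of it. The analysis section then opens the choice to a test of something else. Wilcoxon-Mann-Whitney tests whether a value from one arm tends to exceed a value from the other. It is a test about means only if the two distributions share a shape, and it yields no percentage reduction in the mean.

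Equal shapes are doubtful here. Under Trial intervention, PMPS targets are confined to 0.5 to 2.0 μg/mL, whereas ACPS has no pre-specified limits and is "incremented and decremented by them as they see fit". The pilot SDs also differ.

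Two things are at stake. The trial could be declared significant on a test that does not address its stated criterion. And an open menu of tests in an open-label trial leaves room for the conclusion to depend on which test is reported.

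**Working it through.** **1. Reproduce the plan's figure.** Inputs (Sample size calculation): means 1.580 and 2.231, SDs 0.755 and 0.915, power 90%, two-sided 5%.

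- Difference: 2.231 − 1.580 = 0.651, and 0.651/2.231 = 29.2%.
- Standard error at 36 per arm: √(0.755²/36 + 0.915²/36) = √(0.01583 + 0.02326) = 0.1977.
- Non-centrality: 0.651/0.1977 = 3.29. Satterthwaite degrees of freedom: about 67.6.
- Power from the non-central t distribution: 90.07% at 36 per arm and 89.23% at 35 per arm. So 36 per arm, 72 in total, is the smallest equal allocation that reaches 90%.
- Drop-out: 72/0.90 = 80.

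The stated 72 and 80 are therefore exactly a Welch design.

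**2. Would the choice of test arise?** The pilot coefficients of variation are 0.755/1.580 = 0.48 and 0.915/2.231 = 0.41 for a positive outcome, so right skew is plausible. The documents give no distribution shape, so normal, gamma and lognormal were assumed. Under the planned effect at 36 per arm, a Shapiro-Wilk test at 5% rejects normality in at least one arm in 10%, 68% and 90% of simulated trials respectively.

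**3. What the open choice does.** 10,000 simulated trials per scenario, 36 per arm, pilot SDs.

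| Rejection rate, equal means | Normal | Gamma | Lognormal |
|---|---|---|---|
| Welch | 4.9% | 5.0% | 5.5% |
| Wilcoxon-Mann-Whitney | 4.8% | 5.2% | 5.9% |
| Shapiro-Wilk, then Welch or rank test | 5.0% | 5.7% | 6.1% |
| Smaller of the two p values | 5.9% | 6.6% | 7.6% |
| Tests disagree at 5% | 2.0% | 2.9% | 3.7% |

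The simulation standard error near 5% is √(0.05 × 0.95/10,000) = 0.2 points, so differences of a few tenths should not be read closely. A separate run of 20,000 trials per scenario put the smaller-p-value rule at 6.1 to 7.2%; about 6 to 7% is a fair summary.

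Under the planned effect, the rank test has power of 88.7%, 90.9% and 94.2%, and the two tests disagree in 3.6 to 5.6% of trials.

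**4. What covariates could add.** If covariates explain a share R² of the variance, each SD is multiplied by √(1 − R²). The documents give no R². Assuming 0.10, 0.20 and 0.30, Welch-type power at 72 becomes 92.8%, 95.2% and 97.3%, against 90.1% unadjusted.

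**5. Anaesthetist.** The documents give neither the number of anaesthetists nor an intra-class correlation. Assuming 8 anaesthetists and a correlation of 0.1 or 0.2 in the ACPS arm, simulated type I error for Welch's test is 4.8% or 4.2% when the participating anaesthetists are held fixed with average effect zero. It is 7.8% or 10.2% only when a fresh set of anaesthetists is drawn at random for each trial.

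**The case against.** The best defence is that a journal article condenses a fuller protocol, that the tests are given only as examples, and that an analysis plan not shown here may fix the choice. The article also undertakes to describe and justify any deviation from the original statistical plan. This carries some weight, but it does not remove the mismatch between the article's own sections: one powers on Welch, another offers a rank test for a comparison of means. An open menu also leaves little from which a deviation could be recognised.

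Four stronger readings are tempting, and the document does not support them.

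- *The test is chosen after seeing the data.* Distributional assumptions are usually checked on trial data, so this is a reasonable guess. But the text does not say when the choice is made. It supports only that the test is not fixed.
- *The 5% error rate is broken.* The text describes a choice by assumptions, not by result. On that reading the excess over Welch in the table is 0.1 to 0.7 points. A 9% rejection rate for the rank test can be produced, but only by assuming an SD of 1.3 where the pilot gives 0.755.
- *The unadjusted comparison is wrong.* Randomisation is individual, in blocks of 8, with no stratification factor stated, so an unadjusted comparison is valid. Chance imbalance is already covered by the error rate and the confidence interval. The article does not show that age, sex or joint predict the rate.
- *Ignoring the anaesthetist inflates type I error.* That needs an assumed correlation, an assumed number of anaesthetists and an inference to anaesthetists in general, a target the protocol does not set. For the participating anaesthetists, no inflation appears.

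**Conclusion.** The point holds in a narrow form. The hypothesis, the 29% criterion and the sample size concern means and Welch's test; the Statistical plan leaves the primary test open and names an option that neither tests nor estimates a difference in means. This is an inconsistency within the article, not merely detail deferred to another document.

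The numerical consequence is modest: type I error of about 5 to 6% if assumptions decide, about 6 to 7% if the better p value is taken, and conflicting significance in about 2 to 4% of null trials and 4 to 6% of trials under the planned effect. These figures rest on the pilot SDs, 36 per arm and assumed distribution shapes. The matter of interpretation is weightier: a significant rank test would not establish the mean reduction the trial sets out to show. Since the correction is nearly free, it should be made.

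Covariate adjustment is worth recommending for precision only, and its benefit depends on an R² that the documents do not supply.

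**What to change.** Name one mean-based primary analysis before any outcome data are examined, in all randomised participants. Report the mean difference in mg/kg/h and the percentage reduction in the mean, each with a 95% confidence interval. There are two acceptable forms.

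- **Minimum:** Welch's t test, which matches the sample size calculation and leaves 72 and 80 unchanged.
- **Preferred:** a linear model of the rate on arm, age, sex and hip or knee, with heteroscedasticity-robust standard errors (for example HC3), and unadjusted Welch as supportive. The sample size need not change.

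In either case, state that Wilcoxon-Mann-Whitney is a sensitivity analysis and cannot carry the primary conclusion. A model with an anaesthetist effect in the ACPS arm, using the recorded initials, is an optional further sensitivity analysis.

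The cost is a few sentences in the analysis plan. Every variable is already collected, and no participants or procedures are added.

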## Abstract

**Background:**

The clinical efficacy of effect-site targeted patient-maintained propofol sedation (PMPS) compared to anaesthetist-controlled propofol sedation (ACPS) for patients undergoing awake joint replacement surgery is currently unknown. There is no commercially available medical device capable of delivering PMPS so we have designed and built such a device. We plan a clinical trial to compare PMPS to ACPS and to collect data relating to the safety of our prototype device in delivering sedation.

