The secondary research objectives are:To establish whether patients are less deeply sedated intra-operatively during patient-maintained sedation compared to anaesthetist-controlled sedation.To assess whether patients undergoing PMPS have equal reductions in peri-operative anxiety compared to patients undergoing ACPS.To observe whether patients undergoing PMPS have comparable post-operative satisfaction with their sedation experience compared to patients undergoing ACPS.To explore whether patients who have undergone PMPS are fit for discharge from the post-anaesthetic care unit (PACU) sooner than patients who have undergone ACPS.To determine if patients undergoing PMPS have calculated effect-site concentrations of propofol that are lower than in patients who undergo ACPS.To examine how many times patients using PMPS press their trigger button to increment their dose (successful button press), how many times they press the button while the device is locked out (unsuccessful button press) and whether there is a relationship between pre-operative anxiety state and use of the trigger system.To determine whether patients undergoing PMPS experience a different incidence of airway, respiratory or cardiovascular sedation-related side-effects than patients who have undergone ACPS. Airway sedation-related side-effects include partial or complete airway obstruction that requires the usual clinical anaesthetist to apply one of the following interventions: chin-lift, jaw thrust, nasopharyngeal airway insertion, oropharyngeal airway insertion, laryngeal mask insertion or endotracheal tube insertion. Respiratory sedation-related side-effects are respiratory rate fewer than 8 breaths per minute or arterial oxygen saturations less than 88% in patients with chronic obstructive pulmonary disease (COPD) or 94% in all other patients. Cardiovascular sedation-related side-effects include heart rate or blood pressure reduction greater than 20% from baseline, but such events may be related to spinal anaesthesia rather than the sedation. All such events will be noted by a study investigator and reviewed to determine the likely aetiology. There are no objective clinical criteria to determine this, but routine clinical practice is to assimilate the presented information to estimate the likely contribution from sedation, spinal anaesthesia and/or another cause.To determine whether patients undergoing PMPS experience different health-related quality of life outcomes compared to patients undergoing ACPS.

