### Intervention

The usual clinical care of non-invasive physiological monitoring will be established by the supervising clinical anaesthetist. They will insert an intravenous cannula and spinal anaesthesia will be performed. When satisfied that adequate spinal anaesthesia has been accomplished, they will commence the participant on their allocated sedation regime.

Participants allocated to PMPS will have their sedation infusion commenced at the minimum level of 0.5 μg.mL^− 1^ and will be given the handheld trigger button to press. They will be told *“*Press the button if you want to be more sleepy*”*. Participants allocated to ACPS will be commenced on an effect-site-steered TCI propofol infusion. The supervising clinical anaesthetist will control the effect-site target at their discretion.

Both sedation regimes will commence in the anaesthetic room, prior to the participant moving to theatre. A study investigator will record physiological and sedation outcome measures at 5-min intervals throughout the sedation period.

The sedation regime will be discontinued at the end of surgery when skin clips are applied to the wound. This time will be noted by a study investigator. In the PMPS group the handheld button will be withdrawn from the patient and the TCI infusion stopped. In the ACPS group the TCI infusion will be stopped. If, for any reason, the sedation is discontinued prior to end of surgery, the reason will be noted in a free-text narrative response by a study investigator.

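### The between-arm side-effect comparison is assigned to a complete-case, violation-free set chosen after randomisation, which can bias it and conflicts with the protocol's own drop-out and imputation statements

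*Protocol article*

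**What the plan says.** All references are to the protocol article.

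- **Analysis set for secondary outcomes** (Statistical plan): "We will report analyses of secondary outcomes for complete cases that contain no major clinical investigation plan violations".
- **Side-effects are one of those outcomes** (Study objectives): "To determine whether patients undergoing PMPS experience a different incidence of airway, respiratory or cardiovascular sedation-related side-effects than patients who have undergone ACPS". Airway events are defined by the intervention needed, and respiratory and cardiovascular events by numerical thresholds.
- **Primary outcome** (Statistical plan, directly after the primary test is described): "Testing will be performed using datasets formed according to inclusions based on intention to treat".
- **Drop-outs** (Sample size calculation): "All participants dropping out after randomisation will be included in the study by intention to treat". The same sentence keeps their data, up to the moment of drop-out, for analysis.
- **Missing data** (Statistical plan): "Any missing outcome data will be imputed using either a last-observation-carried-forward rule", or, for some secondary outcomes, replaced by routinely recorded clinical data.
- **Early stopping of sedation** (Intervention): "If, for any reason, the sedation is discontinued prior to end of surgery, the reason will be noted in a free-text narrative response".
- **Safety purpose** (Abstract, Background): one aim is to "collect data relating to the safety of our prototype device in delivering sedation".
- **Attribution of events** (Study objectives): "All such events will be noted by a study investigator and reviewed to determine the likely aetiology". The article concedes that no objective criteria exist for this.

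**The concern.** Whether a participant is a complete case, and whether a major violation has occurred, is known only after randomisation and usually after sedation has begun. Both can depend on how sedation went. Restricting a between-arm comparison to such a set gives up the protection of randomisation for that comparison. The trial is open-label and the intra-operative data collector is unblinded (Trial blinding), so a ruling that something was a major violation could be made knowing both arm and outcome.

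The side-effect comparison is at stake most, because safety data on the prototype device are a stated purpose and a patient with an eventful course is the one whose data must not be lost. The same rule covers depth of sedation, anxiety, satisfaction, readiness for discharge from the post-anaesthetic care unit, effect-site concentration and quality of life.

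**Working it through.** **1. Does the rule reach the side-effect comparison?** The Statistical plan's sentence covers secondary outcomes without exception. Study objectives lists side-effects among the secondary objectives. Only the primary test is assigned to intention to treat. So it does.

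**2. Is the rule consistent with the rest of the text?**

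- *Imputation.* A complete-case set leaves nothing to impute. The imputation sentence cannot be read as confined to the primary outcome, because its second half names secondary outcomes. The two statements, in the same section, cannot both govern those outcomes.
- *Drop-outs.* A participant who drops out after randomisation with partial data is kept for analysis under Sample size calculation, but is not a complete case under Statistical plan. The statements agree only if the former is read as applying to the primary outcome alone, which it does not say.

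**3. How large could the bias be?** The plan gives no figure for this, so what follows is an illustration on assumed rates.

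Inputs from the article: 72 evaluable participants and 10% drop-out, hence 72/0.9 = 80 randomised, or 40 per arm at 1:1. (The 72 reproduces: Welch power is 90.07% at 36 per arm and 89.2% at 35. The point does not rest on it.)

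Let *n* = 40 be the arm size, *p* the true event rate in both arms, *x* the number excluded from one arm only, and *q* the share of those excluded who had an event. Then

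- observed rate in that arm = (*np* − *xq*)/(*n* − *x*)
- spurious difference = observed rate − *p* = *x*(*p* − *q*)/(*n* − *x*)

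The second expression is zero when *q* = *p*, that is, when exclusion is unrelated to events.

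| *p* | *x* | *q* | Observed rate | Spurious difference (points) |
|---|---|---|---|---|
| 30% | 4 | 100% | 8/36 = 22.2% | −7.8 |
| 30% | 4 | 75% | 9/36 = 25.0% | −5.0 |
| 30% | 4 | 50% | 10/36 = 27.8% | −2.2 |
| 30% | 4 | 30% | 10.8/36 = 30.0% | 0 |
| 30% | 4 | 0% | 12/36 = 33.3% | +3.3 |
| 30% | 2 | 100% | 10/38 = 26.3% | −3.7 |
| 30% | 6 | 100% | 6/34 = 17.6% | −12.4 |
| 10% | 4 | 100% | 0/36 = 0% | −10.0 |
| 50% | 4 | 100% | 16/36 = 44.4% | −5.6 |

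A negative value flatters whichever arm lost the patients. With equal numbers and equal event shares excluded from both arms, the difference is again zero. An analysis of all randomised participants gives zero in every row.

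**The case against.** The strongest reply has four parts.

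**The article does not say who is excluded.** Major violation is undefined, and a condensed article may leave that to the full protocol. The Safety section allows the anaesthetist, in either arm, to alter sedation depth when a patient is disinhibited in a disruptive or dangerous way, so such a change need not be a violation. Early stopping is recorded but not classed as one. This stands. A reader might infer that the rule removes the patients in whom sedation failed, but the text supports only that it may do so, for instance where their data are incomplete.

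**The direction is not established.** A reader might infer that the bias favours the device, because PMPS follows a fixed algorithm while ACPS has no preset limits to breach. That is a conjecture. The PMPS limits are part of how the drug is delivered, and discretionary changes are allowed in both arms. This also stands.

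**Safety data are reported elsewhere.** All collected data are to be summarised descriptively (Statistical plan), and adverse events and device events are recorded and reported (Safety). That reduces the risk of events going unseen. It does not supply the randomised between-arm comparison that Study objectives promises.

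**A violation-free set can be the stricter one.** The anxiety objective speaks of equal reductions and the satisfaction objective of comparable results. Where similarity is the hoped-for result, dilution from non-adherent patients can favour it. This is a good reason to report the violation-free set alongside for those two outcomes, but not to make it the only set for side-effects.

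On attribution, a reader might infer that an unblinded investigator sorts events by cause and that those ascribed to the spinal anaesthetic are dropped. The article does not identify the reviewer and does not say that any event is dropped. What remains is that cause is judged without objective criteria and no blinded review is described.

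**Conclusion.** The concern holds as a defect in a stated rule. The article assigns the side-effect comparison, with every other secondary outcome, to a set selected after randomisation, and that assignment contradicts its imputation sentence and is at odds with its drop-out statement.

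The rule can bias the comparison; the documents do not show that it will, by how much, or in which direction. On the assumptions tabulated (40 per arm, equal true rates, 2 to 6 exclusions in one arm only), the spurious difference runs from −12.4 to +3.3 percentage points, and is zero if exclusion is unrelated to events. Those event and exclusion rates are assumed. At this sample size a handful of exclusions can move the result by several points.

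The primary outcome test and the sample size are not affected.

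**What to change.** 1. Reconcile the complete-case sentence with the imputation sentence in Statistical plan and the drop-out sentence in Sample size calculation, so that one analysis set and one missing-data rule is stated for each outcome.
2. Compare side-effects by allocated arm in all randomised participants who started sedation. Count every event that meets the definitions in Study objectives, whatever cause is assigned to it; randomisation balances the spinal contribution in expectation. Report counts by attributed cause as supportive.
3. Analyse the other between-arm secondary outcomes by allocated arm in all randomised participants with available data, and button-press outcomes in all PMPS participants who started sedation.
4. Keep the complete-case, violation-free set as a supportive analysis, and report it alongside the main one for anxiety and satisfaction, where the aim is similarity.

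The cost is a change of wording and a few extra tables. The data are already to be collected, and the sample size does not change. The drawback is some dilution from non-adherent patients, which item 4 makes visible.
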